### Secondary outcome measures

#### Child social understanding

Child theory of mind is assessed using a set of 10 tasks adapted from the scale developed by Wellman and Liu [70] and used extensively across a range of countries and contexts [25, 30, 70, 71]. The tasks gradually become more complex, beginning with tasks assessing understanding of diverse desires, and moving on to tasks require understanding of diverse beliefs, knowledge access, and false belief. A total score is calculated from the correct answers. This assessment is made at all three assessment points.

Emotion recognition is measured using a set of eight illustrated pictures of children with four different emotional expressions: happy, angry, sad, and frightened. Pictures are presented on a computer screen in blocks of four showing all emotions. The assessor then asks the child to identify certain expressions, e.g. ‘show me the happy boy’. A total score will be calculated from their responses. Emotion recognition and understanding tasks will be administered at the final follow-up. These tasks have been specially designed for the current project, but are based on assessments successfully used by Taumoepeau and Ruffman [72].

#### Parental sensitivity and reciprocity

Parental sensitivity and reciprocity are assessed by direct observation of the parent and child during book-sharing and non-book-sharing contexts. Parent-child interactions are videotaped and independently coded using a reliable system [73], shown in our previous trial to improve with book-sharing training and to mediate the effects of the intervention on child cognitive development [45, 46]. These variables are also rated in the ‘clean-up’ task. All these assessments are made at all three assessment points.

#### Parental discipline

Parenting is assessed using the Discipline and Violence Self-report Questionnaire [74]. This questionnaire comprises 13 items of discipline practice (including violent ones), as well as an assessment of the belief in the necessity of physical punishment in order for children to learn respect for adults. Parental disciplining strategies are also assessed by direct observation of videos of interactions during the prohibition and compliance tasks. Carer behaviour is coded using measures of harsh/coercive discipline (physical and verbal), and supportive guidance (physical and verbal). This assessment of parental discipline has been widely used in the assessment of parenting in several HICs [65, 66]. Since, to our knowledge, they have not been used in a LMIC context, baseline videos will be examined and culturally sensitive modifications will be made to existing coding schemes [66].

### Exploratory outcomes

#### Mental state talk

Parental mental state talk will be assessed by making transcripts (and translating them into English) from video-recordings of interactions during book-sharing, and during a narrative cartoon explanation task. The latter task is one previously used to assess child theory of mind [70, 71]. We show the carer two sets of six cartoon pictures, showing a sequence in which a cartoon character is unaware of another character who is attempting to perform a malevolent act (e.g. a cat attempting to raid a bird’s nest). The carer is asked to tell the child what is happening in the cartoon. Mental state talk will be coded based on a system derived from Ruffman and colleagues [40, 72, 75]. Baseline data will be used to develop a culturally sensitive coding system.

#### Home language environment

In a subsample, the child’s home language environment is assessed using the LENA digital recording system that captures language heard by the child over the course of a typical day. The LENA analysis software produces automated measures of adult word counts that represent the number of words that a child hears from adult men or women during the period of recording. Though predominantly used in HIC contexts, LENA has been used successfully in a low-income context in Senegal [76].

#### Physiological response to emotion

In a subsample, child physiological response to different emotional faces (i.e. pictures of happy, sad, fearful or angry children) is assessed at the pre-intervention and follow up assessment. This is done using a functional infrared thermal imaging (fIRT) camera that converts infrared light into temperature, thereby allowing wireless monitoring of autonomic nervous system responses [77]. We will be recording sympathetic cutaneous reactions to the presentation of images displaying different emotions [78].

### Potential moderators

#### Parental stress

The Parenting Stress Index (short form) [79] is administered. This is a 36-item scale that measures stress associated with the role of parenting that has been used successfully in the South African context [80]. It is administered to the carers at all three assessment time points. In addition, we use, as a potential moderator, an index of socioeconomic adversity, previously found to moderate the impact of a home-visiting intervention in infancy on child cognitive outcome [46].

#### Caregiver mental health

The mental health of the carers is assessed using the Patient Health Questionnaire-9 (PHQ9) [81]. This 10-item questionnaire asks caregivers about depressive symptoms experienced over the previous 2 weeks. It is a multipurpose instrument for screening, diagnosing, and monitoring depression levels, and has been used successfully in previous South African research [82].

#### Intimate partner violence

Caregivers are being questioned on exposure to intimate-partner violence, at all three assessments points, using questions from the measure developed for the WHO multicountry study on women’s health and domestic violence [83].

### Data management

Data are collected on tablets and, once complete, automatically submitted to a secure server platform hosted by Mobenzi, a South African organisation that specialises in software development for research purposes. Participants are allocated personal identification numbers that are used in all study records to protect their identity and maintain confidentiality. All child assessments and caregiver-child interaction tasks are video-recorded, for both coding and quality control purposes. Videos are labelled by ND and saved in a separate location at the end of each day. In addition, a random subsample (10%) of videos is checked by ND for fidelity to the assessment procedure. Data transmitted from the tablets are stored on a secure central network server.

### Data analysis

Data analysis will be completed by a designated statistician/statistical team independent from study investigators. Group baseline differences will be assessed using independent *t* tests and Mann-Whitney *U* nonparametric tests if data do not fit necessary assumptions. Analysis of baseline group differences will also include sociodemographic data such as gender and household factors (e.g. income, employment). Analysis of covariance will be used to assess intervention effects at post intervention and follow-up. Post-test and follow-up scores for primary and secondary outcomes will constitute dependent variables, while child age, sex and baseline scores will be controlled for as covariates. Intention-to-treat analysis will be used to examine intervention effects. Missing individual-level outcome data will be addressed using multiple imputation methods.

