#### Power calculation

All power calculations have been run for 80% power and alpha = 0.05. The power calculation for primary outcomes of language and attention was based on previous research that aimed to improve child language and focal attention through a book-sharing intervention in South Africa [45]. The effect size on sustained attention was *d* = 1.1, and the effect size on receptive language was *d* = 0.73. Based on these figures, two groups of 13 are sufficient to detect the established difference on the attention variable, and two groups of 44 are sufficient to detect the established difference on the language variable. For the behavioural outcomes of aggression and prosocial behaviour, the power estimates were based on normative data from a study in Khayelitsha on a sample of 302 children. For prosocial behaviour the mean was 7.39 (SD = 2.08) and for aggression it was 12.84 (SD = 7.18). As such, for both the prosocial and the aggression variables, two groups of 64 are sufficient to detect the difference (two-tailed), based on an effect size of 0.50. Two groups of 70 are, therefore, being recruited, which allows for 10% sample attrition.

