### Intervention

The intervention is a group-based, dialogic book-sharing programme based on our previous programme [45, 46, 49]. The intervention consists of 60–90-min sessions run weekly for eight consecutive weeks. The programme is delivered to groups of three to six caregivers and their children. Each session focusses on different and incremental techniques for caregivers to apply during book-sharing. For the first six sessions there is a ‘book of the week’ that the carers take home to share with their child, and that they bring back the following week. In session 7 all the key principles are reviewed, and the child chooses which of the six books they want to take home for that week. During the final, eighth, session, there is a group discussion where caregivers are guided in reflecting on the programme and they discuss plans for continuing with their book-sharing – such as registering at a nearby children’s library or continuing to meet as a group. Session 8 ends with a graduation where caregivers are presented with a certificate of completion, a laminated card with a summary of the key lessons from the programme (on the back of which there is a picture of themselves and their child sharing a book), and a copy of each of the six books used in the programme. Table 1 details the content for each session. For the 6-month period following session 8, the facilitator visits each participant bi-monthly to deliver a new picture book and have a short encouraging conversation with the caregiver about their book-sharing.

**Table 1 Tab1:** Summary of intervention session content

Session	Session content
1	*Introduction to Book-sharing*
	Introduction and basic dialogic book-sharing skills part 1 – following the child’s lead, using a lively voice, setting up book-sharing routines
2	*Pointing and Naming*
	Basic dialogic book-sharing skills part 2 – pointing and naming, repeating, extending and elaborating on things that interest the child, finding opportunities for praise
3	*Naming and Linking*
	Asking ‘where/who/what’ questions, linking book content to the child’s own experience, finding opportunities to use actions (e.g. hugging, eating)
4	*Talking about Feelings*
	Helping the child understand the meaning of basic emotion terms: happy, sad, angry, scared. Discussing why book characters feel the way they do, using facial expression and tone of voice to convey a character’s feelings, linking feelings to the child’s own experience
5	*Talking about Intentions*

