### Intervention facilitators, training and supervision

The intervention is delivered by two isiXhosa-speaking women from Khayelitsha. Both these facilitators have experience delivering book-sharing training to mothers from the community, having been facilitators in our previous trial [45, 46], as well as in an earlier pilot study [49]. Each of the two facilitators is supported by an assistant during intervention sessions whose role is to look after the children, who also attend the sessions. The assistants were selected from the community, based on having previous experience working with young children.

Facilitator training for the current book-sharing intervention was held over a 2-day workshop, run by PC, LM and ND. This included a refresher session, when the content of the earlier programme was reviewed, including a review of the accompanying PowerPoint presentation materials and videos. This was followed by instruction on the new programme content and materials. First, the key principles of the new sessions (i.e. those concerning emotions, intentions and perspectives – see Table 1) were explained, and the accompanying illustrative videos viewed. This was followed by discussion between the trainers and facilitators, and any questions or uncertainties were resolved. During these discussions the facilitators also discussed ways in which the key principles of the new material could be explained and demonstrated in a culturally appropriate manner.

The second part of the facilitator training covered the one-to-one sessions where parents practise book-sharing with their children and receive feedback from the facilitator. This training specified the role that the facilitator needs to play during these sessions, covering principles of sensitive instruction, modelling, and providing positive support. Additionally, facilitators were instructed on how to incorporate into the one-to-one sessions the central take-home messages from the group session.

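### Only the intervention arm is treated in small groups, yet the ANCOVA and the sample size assume independent dyads; standard errors are too small if outcomes correlate within book-sharing groups, and 80% power is not assured for aggression and prosocial behaviour

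*Protocol article*

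**What the plan says.** - **Randomisation.** Under Study design and Randomisation, individual dyads are allocated 1:1 to the intervention or to a wait-list control. Controls are offered the programme only after all three assessment waves.
- **Delivery.** Under Intervention: "The programme is delivered to groups of three to six caregivers and their children". There are eight weekly sessions. Each also has a one-to-one part with the facilitator, who later makes individual visits over the six months after session 8. Under Intervention facilitators, training and supervision: "The intervention is delivered by two isiXhosa-speaking women from Khayelitsha".
- **Analysis.** Under Data analysis: "Analysis of covariance will be used to assess intervention effects at post intervention and follow-up". The listed covariates are child age, sex and baseline score. Mixed linear models are named only under Moderator analysis, for exploring mediators and moderators.
- **Sample size.** Under Power calculation: "All power calculations have been run for 80% power and alpha = 0.05". For the two behavioural outcomes, "two groups of 64 are sufficient to detect the difference (two-tailed), based on an effect size of 0.50". Seventy per arm are recruited to allow for 10% attrition. No ICC or design effect is given.

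**The concern.** Intervention families who share sessions, peers and a facilitator may end up more alike than families in different groups. Controls share nothing comparable, so the correlation arises in one arm only. A model that treats intervention dyads as independent then understates the variance of that arm's mean, and so the standard error of every treatment contrast. Intervals would be too narrow and the nominal 5% test would reject too often, for primary and secondary outcomes alike. The same omission makes the sample size look more secure than it is. That matters most for aggression and prosocial behaviour, because they set the sample size and have no slack.

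**Working it through.** **Inputs from the protocol.** Two-sided alpha 0.05 and 80% power; d = 0.50 with 64 per arm (behavioural outcomes); d = 1.1 (attention) and d = 0.73 (language); 70 per arm recruited, 10% attrition; group size m from 3 to 6 (midpoint 4.5); two facilitators.

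**Assumed.** Group-level ICC of 0.02 to 0.10. The protocol gives none.

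**Step 1: the plan's own figures.** With independent observations, n per arm = 2(1.96 + 0.8416)²/d² = 15.70/d².
- d = 0.50: 62.8, so 63. The exact t calculation gives 64, with power 80.1%. This reproduces the stated 64 with no allowance for clustering.
- d = 1.1: 12.97, so 13 (normal approximation). Reproduces.
- d = 0.73: 29.5, so 30. The stated 44 does not follow from this effect size, but it errs on the safe side and does not set the sample size.
- Attrition: 70 × 0.9 = 63 per arm, which gives 79.5% at d = 0.50. The behavioural outcomes start with no margin.

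**Step 2: clustering in one arm.** The design effect in the intervention arm is DE = 1 + (m − 1) × ICC. The control arm has 1. The variance of the difference is inflated by V = (1 + DE)/2, and the true standard error is √V times the naive one. Approximate type I error of the naive test is 2[1 − Φ(1.96/√V)]. Power is that of a two-sided t test with effect d/√V, 64 per arm and no credit for baseline adjustment.

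| m | ICC | DE | V | √V | Type I error | Power, d = 0.50 |
|---|---|---|---|---|---|---|
| 3 | 0.02 | 1.04 | 1.020 | 1.010 | 5.2% | 79.4% |
| 3 | 0.05 | 1.10 | 1.050 | 1.025 | 5.6% | 78.2% |
| 3 | 0.10 | 1.20 | 1.100 | 1.049 | 6.2% | 76.3% |
| 4.5 | 0.02 | 1.07 | 1.035 | 1.017 | 5.4% | 78.8% |
| 4.5 | 0.05 | 1.175 | 1.0875 | 1.043 | 6.0% | 76.8% |
| 4.5 | 0.10 | 1.35 | 1.175 | 1.084 | 7.1% | 73.5% |
| 6 | 0.02 | 1.10 | 1.050 | 1.025 | 5.6% | 78.2% |
| 6 | 0.05 | 1.25 | 1.125 | 1.061 | 6.5% | 75.4% |
| 6 | 0.10 | 1.50 | 1.250 | 1.118 | 8.0% | 70.9% |

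With 63 per arm, power is 0.6 to 0.7 points lower in every row.

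**Step 3: the other primary outcomes.** In the worst row (m = 6, ICC 0.10, 64 per arm), power is 95.6% for language at d = 0.73 and above 99.9% for attention at d = 1.1.

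**Step 4: what baseline adjustment could recover.** If the baseline score correlates r with the outcome, and residual variance falls by 1 − r² while the ICC stays the same, the loss is cancelled when r = √(1 − 1/V). That is r = 0.28 at m = 4.5 and ICC 0.05, 0.33 at m = 6 and ICC 0.05, and 0.45 at m = 6 and ICC 0.10. Less favourably, if only the non-clustering part shrinks, the variance factor is (1 − r²) + (m − 1) × ICC/2. At m = 4.5 and r = 0.3, power is then 80.2% at ICC 0.05 and 76.9% at ICC 0.10; at r = 0.5 it is 86.6% and 83.1%. The protocol gives no r.

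**The case against.** **A reader might infer that the trial does not deliver its stated power. The documents do not support that.** Language and attention stay above 95% in every row above. For the behavioural outcomes the sample size took no credit for the baseline score that the ANCOVA includes, and a correlation of about 0.3 would offset an ICC of 0.05. Both the ICC and this correlation are unknown, so it would be one-sided to count only the unfavourable one. This objection stands. It does not remove the standard error problem, because baseline adjustment does not correct for whatever within-group correlation remains afterwards.

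**The type I error excess is conditional.** If the programme affected nobody, sitting in a group would add no correlation beyond what individual randomisation balances, and the test would hold about its nominal level. The excess needs groups that shift outcomes around a zero mean effect. It is also small at low ICC, and part of the treatment is individual rather than group-based. This stands as a limit on size. Interval coverage still suffers whenever groups differ in their effect.

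**A reader might also count the two facilitators as a further source of error.** With only two, a facilitator variance cannot be estimated, and the result is naturally conditional on these two. That limits generalisation; no model proposed here cures it, so it carries no weight in the size given.

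**The analysis plan, not shown, may handle this.** It may. But the article does more than leave the matter open: it names the model and its covariates and fixes a sample size, all on independence.

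**Conclusion.** The point holds in a limited form. The design is partially nested, and neither the named ANCOVA nor the power calculation allows for it. Under any positive within-group correlation in the intervention arm, the stated analysis gives standard errors that are too small: by a factor of 1.01 to 1.12 for an assumed ICC of 0.02 to 0.10 and groups of 3 to 6, with type I error of about 5.2% to 8.0%. On the protocol's own basis, power for aggression and prosocial behaviour is about 79% to 71%. So 80% is not assured for these two outcomes; whether it is missed depends on an ICC and a baseline-outcome correlation that the protocol does not give. At an ICC of zero there is no error. The calculation assumes equal group sizes, stable group membership and no loss of degrees of freedom. The text does not say that groups were fixed, and catch-up sessions were planned for missed ones.

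**What to change.** 1. **Main analysis.** Keep the ANCOVA covariates and account for book-sharing group in the intervention arm, with each control dyad as its own cluster. Either a random intercept for group with small-sample degrees of freedom, or cluster-robust standard errors with a small-sample correction, is adequate. Name one before outcome data are analysed.
2. **Group membership.** Analyse each intervention dyad in its originally scheduled group, whatever catch-up sessions it attended.
3. **Facilitators.** Show results by facilitator, and state that facilitator variance cannot be estimated with two.
4. **Power.** Restate power for aggression and prosocial behaviour over an ICC range, and state any baseline-outcome correlation assumed.

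**Cost.** Intervals become slightly wider and the stated power less favourable. Recruitment is reported as ended in August 2016, so restating power informs interpretation and does not change the sample size. The change needs no new data if group membership can be recovered from the attendance and scheduling records that facilitators keep. The protocol does not say outright that it is recorded, so this should be checked first.

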#### Mediator analysis

Mediator analysis will aim to identify certain active components of the intervention and elucidate the pathways to change. To this end, the following two questions will be examined: whether improvements in maternal sensitivity and reciprocity in the book-sharing context mediate improvements in child language and attention; and whether increases in maternal sensitivity and mental state talk in both book-sharing and non-book-sharing contexts, and reduction in negative parenting and increase in supportive parenting, mediate improvements in child social understanding, prosocial behaviour, and aggression.

#### Moderator analysis

An exploratory subgroup analysis will be conducted to investigate whether certain groups benefit more or less from the intervention. Subgroup analysis will be explored for carer relationship (mother, father, grandparents), child sex, number of sessions attended, family socioeconomic adversity, parental stress, and caregiver mental health. Potential mediators and moderators of the intervention will be explored using mixed linear models.

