**Fig. 1 Fig1:**
[figure not shown]
Schedule of enrolment, interventions and assessments. Standard Protocol Items: Recommendations for Interventional Trials (SPIRIT) figure displaying schedule of enrolment, interventions and assessments

Hypotheses:

Primary hypotheses:Compared to control-group children whose carers receive no intervention, those whose carers receive the programme will evidence significantly better outcomes on measures of language and sustained attentionCompared to control-group children, intervention-group children will evidence significantly more prosocial behaviour and less aggression

Secondary hypotheses:3.Compared to control-group children, intervention-group children will evidence significantly better social understanding4.Compared to control-group caregivers, caregivers who receive the programme will evidence significantly more sensitivity, reciprocity, and mental state talk with their children, both in book-sharing and non-book-sharing contexts5.Compared to control-group caregivers, caregivers who receive the programme will evidence significantly less negative and more supportive parenting in challenging contexts6.Improvements in child language and attention will be mediated by improvements in maternal sensitivity and reciprocity in the book-sharing context, and7.Improvements in child social understanding, prosocial behaviour and aggression will be mediated by increases in maternal sensitivity and mental state talk in both book-sharing and non-book-sharing contexts, and by a reduction in negative parenting and an increase in supportive parenting in challenging contexts

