### Randomisation

Eligible participants who consented to taking part in the study were randomised in a 1:1 ratio to the index group and a wait-list control condition (the latter being offered the intervention once the three waves of assessment have been completed). A minimisation process was used to ensure a similar distribution of participant characteristics between the two study groups in terms of child age (younger (23–25 months) and older (25–27 months) and sex. ND performed the minimisation process, using the MINIM software [48] on site, when participants consented to being part of the study and prior to completion of baseline assessments. ND then notified an isiXhosa-speaking research assistant of the allocation, and this assistant then privately explained the allocation to the participant. The allocation list is held by ND, and is inaccessible to any of the staff or partners involved in the assessment or coding.

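### Number of sessions attended is listed as an exploratory moderator, but it arises after randomisation and does not exist in the wait-list arm, so its interaction with arm cannot be estimated and any attendance contrast is open to selection bias

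*Protocol article*

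**What the plan says.** The Moderator analysis section sets out its aim: "An exploratory subgroup analysis will be conducted to investigate whether certain groups benefit more or less from the intervention". After carer relationship, the variables to be explored are "child sex, number of sessions attended, family socioeconomic adversity, parental stress, and caregiver mental health". The only method given is one sentence: "Potential mediators and moderators of the intervention will be explored using mixed linear models".

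Three other places fix what attendance is.

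- **Timing of allocation.** Under Randomisation, minimisation was run "when participants consented to being part of the study and prior to completion of baseline assessments". Under Intervention, eight weekly sessions follow, so every attendance value comes after allocation.
- **Access in the control arm.** Randomisation describes the wait-list group as "the latter being offered the intervention once the three waves of assessment have been completed".
- **Definition of the comparison.** The first primary hypothesis reads "Compared to control-group children whose carers receive no intervention".

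On the list of moderators, Table 2 names parental stress, caregiver mental health and intimate partner violence. The Potential moderators section covers the same three and adds an index of socioeconomic adversity. For partner violence it says "Caregivers are being questioned on exposure to intimate-partner violence, at all three assessments points". The Moderator analysis list has no entry for partner violence.

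**The concern.** A moderator analysis asks whether the difference between arms changes across levels of a characteristic. The characteristic must therefore take values in both arms and must not be a consequence of allocation. Child sex, carer relationship and socioeconomic adversity can meet that condition. Sessions attended cannot: it is produced by the intervention arm's contact with the programme and has no counterpart among controls.

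If the listed analysis is run anyway, it becomes a contrast that randomisation does not protect. Carers who come to most sessions may differ in motivation, stress or working hours from those who come to few, and their children may differ for the same reasons. A gradient of outcome on sessions could then appear without any effect of the sessions. In a trial of an eight-session programme that the Discussion describes as brief and readily deliverable, such a gradient is easily read as evidence on how much of the programme is needed.

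**Working it through.** **1. Can the interaction be estimated?** Let T be arm (1 intervention, 0 control) and A sessions attended (0 to 8, from the Intervention section). By the Randomisation section, A = 0 for every control throughout the outcome period. A moderator model needs the four columns 1, T, A and T×A. When T = 0, A = 0 and T×A = 0. When T = 1, T×A = A. The columns A and T×A are therefore identical, and the design matrix has rank 3, not 4 (confirmed numerically with 70 per arm). Main effect and interaction cannot be separated. If one is dropped, the remaining coefficient is simply the slope of outcome on attendance within the intervention arm. A mixed linear model does not change this.

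**2. How large could selection be?** The article states no figure for this analysis, so there is none to reproduce. The following are illustrations with a true effect of zero.

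*Assumption set A.* A carer trait correlates 0.4 with attendance and 0.5 with the child outcome, and attendance is continuous and split at its median.

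- Attendance-outcome correlation: 0.4 × 0.5 = 0.20.
- A normal variable split at its median has half-means at ±√(2/π) = ±0.798 SD. High attenders therefore lie 0.798 × 0.20 = 0.16 SD above controls and low attenders 0.16 SD below.
- Gap between high and low: 2 × 0.16 = 0.32 SD. Simulation with 70 per arm gave 0.316.

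*Baseline adjustment.* The Data analysis section adjusts the outcome analyses for baseline score, age and sex. Suppose the moderator models do the same for baseline score, and that the trait correlates 0.5 with baseline as well. With baseline-outcome correlation r, and the high/low indicator correlated 0.798 × 0.20 = 0.160 with both scores, the adjusted gap is 0.160 × (1 − r) / (1 − 0.160²) / 0.5, which is about 0.33 × (1 − r).

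| r | Adjusted gap (SD) |
|---|---|
| 0.3 | 0.23 |
| 0.5 | 0.16 |
| 0.7 | 0.10 |

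Simulation gave 0.23, 0.16 and 0.10.

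*Assumption set B.* Attendance is binomial out of 8 with mean about 5.9 and follows carer engagement closely (correlation about 0.83). There is no baseline adjustment, 70 carers in the intervention arm, and 3,000 simulated trials per setting.

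| Engagement-outcome correlation | Null trials with a significant attendance slope (two-sided 0.05) | Gap, 7–8 sessions versus fewer (SD) |
|---|---|---|
| 0 | 5% | about 0 |
| 0.1 | 10% | 0.07 + 0.07 = 0.14 |
| 0.2 | 29% | 0.15 + 0.14 = 0.29 |
| 0.3 | 55% | 0.21 + 0.22 = 0.43 |

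The gap is the high-attender excess over controls plus the low-attender deficit. With 63 carers (10% attrition) the rejection rates are 5%, 10%, 26% and 51%.

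**3. The moderator lists side by side.**

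| Variable | Table 2 | Potential moderators | Moderator analysis |
|---|---|---|---|
| Parental stress | yes | yes | yes |
| Caregiver mental health | yes | yes | yes |
| Intimate partner violence | yes | yes | no |
| Socioeconomic adversity | no | yes | yes |
| Carer relationship, child sex | no | no | yes |
| Sessions attended | no | no | yes |

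No two of the three lists agree. Sessions attended appears only in the last.

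**The case against.** The strongest reply is that little hangs on this analysis. It is labelled exploratory, no hypothesis concerns attendance, and intervention effects are judged by intention to treat. That stands, and it limits the severity.

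The exact attendance contrast is also unstated and may be set out in an analysis plan that is not shown. That stands for the form of the model but not for the choice of variable. The article commits to attendance as a moderator, and no specification makes its interaction with arm estimable.

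Catch-up sessions, described under Intervention facilitators, training and supervision, may narrow the spread of attendance, and baseline adjustment shrinks the bias. Both are fair. Neither removes the selection.

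Three stronger readings are tempting, and the documents do not support them:

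- A reader might infer that any attendance result would be nothing but selection bias presented as a dose effect. The article makes no dose-effect claim, and a real gradient could be mixed in. The supportable statement is that the result is open to selection bias.
- A reader might set the 0.32 SD gap against the 0.50 in the Power calculation section and call it about 60% of the design effect. That divides a high-versus-low attender gap by an intervention-versus-control effect. The like-for-like figure under set A, unadjusted, is 0.16 / 0.50 = 32%.
- Of the Parenting Stress Index the article says "It is administered to the carers at all three assessment time points", and a reader might infer that post-baseline values will serve as moderators. Repeated measurement is not a plan to moderate on later values, and the choice of wave is detail that an analysis plan may hold.

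**Conclusion.** The point holds as a limited one. Sessions attended cannot act as a moderator of the arm effect, because it follows randomisation and is absent in the wait-list arm until all assessments are done. This rests on the article's own design statements and on no assumed figure.

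The size of the possible bias does rest on assumptions. With no true effect and moderate correlations (0.4 and 0.5), high and low attenders would differ by roughly 0.1 to 0.3 SD, depending on baseline adjustment. It would be larger if attendance followed engagement more closely, and nil if engagement were unrelated to outcome. None of these correlations comes from the documents.

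The intention-to-treat comparisons are not affected. A reader might infer that the fault weakens the trial's main conclusions or would steer roll-out of the programme, but nothing in the article gives this exploratory analysis that role. The omission of intimate partner violence from the Moderator analysis list is a separate and minor inconsistency.

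**What to change.** In the Moderator analysis section, remove number of sessions attended from the subgroup list. Report attendance descriptively, or as an analysis within the intervention arm that is explicitly labelled observational.

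A complier-average (instrumental-variable) analysis with allocation as instrument is optional. It assumes that allocation acts only through the sessions. At 6 months that assumption is strained, because the Intervention section has the facilitator visiting participants bi-monthly after session 8 with a new book and a short encouraging conversation. If the analysis is done, either limit it to the post-intervention assessment or state that these visits give allocation a second route to the 6-month outcome.

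Separately, reconcile the moderator lists. State whether intimate partner violence is a moderator, and do so without dropping carer relationship, child sex or socioeconomic adversity. Simply making the Moderator analysis section match Table 2 would drop those three.

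The cost is wording only, since facilitators already track attendance. What is given up is an attendance subgroup result that could not have answered the question put to it. The optional complier analysis would give wide intervals.
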